#### Power Calculation

Due to the anticipated difficulties in recruitment that will likely arise from the complexities of running a study during a pandemic and the time-sensitive nature of implementing an early sleep intervention relative to both the start of the pandemic and insomnia symptoms, we view this trial as a feasibility study. Therefore, for this feasibility trial, we aimed to recruit a total of 50 subjects, which would result in 25 subjects in each study group. With this sample size, our power calculations were derived using the 2-group *t* test of equal means based on the difference between CBT-I and waitlist control group at 28 weeks, at a 5% level of significance. With 25 per group, the study is 80% powered to detect a large effect size (Cohen d=0.80).

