#### Randomization

Participants were randomized into either CBT-I or a 28-week waitlist control condition using stratification by biological sex at birth (male, female) and baseline insomnia severity (ISI ≥10, ISI <10) in a 1:1 ratio. Participants who dropped out of the study after randomization, but before the week 1 visit, were replaced in the randomization matrix. Our sample size estimates (see the Power Calculation section) accounted for this replacement.

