## Results

### Trial Status and Timeline

The trial began recruitment on June 4, 2020, and the first participant was consented on June 10, 2020. As of October 2021, 794 subjects had completed prescreening, and 96 subjects had completed a Zoom screening session. A total of 49 participants were randomized to a study group (26 to the CBT-I group and 23 to the waitlist control group). Overall, 38 participants had completed the week 6 follow-up, 37 had completed the week 12 follow-up, 34 had completed the week 28 follow-up, and 15 had completed the week 56 follow-up. At the time of this writing, there were an additional 3 participants awaiting the 28-week follow-up and a total of 23 participants awaiting the week 56 follow-up (13 in CBT-I and 10 in waitlist control group). The study closed to enrollment of new subjects on June 17, 2021. As of the writing of this paper, due to the outstanding data collection of the remaining 28- and 56-week data, we had conducted interim analyses for the week 6 follow-up but had not tested the results of our primary hypotheses in full. We expect primary results of the study to be published in 2022.

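### The 80% power for d=0.80 at week 28 assumes that all 25 recruited per group are analysed there; the article's own counts allow at most 37 in total, for which the same t test has at most about 66%

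*Protocol article*

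**What the plan says.** The Power Calculation section sets the target: "we aimed to recruit a total of 50 subjects, which would result in 25 subjects in each study group". Power is computed for a two-group t test "based on the difference between CBT-I and waitlist control group at 28 weeks", "at a 5% level of significance", and the result is given as "With 25 per group, the study is 80% powered to detect a large effect size (Cohen d=0.80". Sidedness is not stated.

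The Randomization section has the only provision for loss: "Participants who dropped out of the study after randomization, but before the week 1 visit, were replaced in the randomization matrix". It adds: "Our sample size estimates (see the Power Calculation section) accounted for this replacement". No rate of loss after week 1 appears in either section.

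Trial Status and Timeline reports 49 randomised (26 CBT-I, 23 waitlist), 38 completing week 6 and 37 completing week 12. At week 28, "34 had completed the week 28 follow-up", with "an additional 3 participants awaiting the 28-week follow-up". Enrolment closed on June 17, 2021.

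The statistical section puts effect sizes and confidence intervals ahead of significance tests. The Discussion concedes reduced power, which it attributes to recruitment. It also names unequal attrition as a possible limitation and says long-term comparisons could lack power. It quantifies none of this.

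**The concern.** The number recruited and the number analysed at week 28 are the same in the power statement. That holds only if nobody is lost between the week 1 visit and week 28. The same article reports counts showing that 25 per group at week 28 can no longer be reached, yet the power sentence stands without qualification.

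Two things are at stake. A reader who takes the 80% at face value will read too much into an inconclusive week 28 comparison. And the article says its findings will guide larger trials, so planners need the precision the trial can actually deliver. No precision figure is given, although estimation is the declared emphasis.

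**Working it through.** **Inputs.** From Power Calculation: d = 0.80, alpha 5%, 25 per group, two-group t test at week 28. From Trial Status and Timeline: 49 randomised (26/23), 34 completed week 28, 3 awaiting it. The split by arm at week 28 is not given, so a range is shown.

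**Formulas.** For group sizes n1 and n2 and a difference in SD units:
- SE = sqrt(1/n1 + 1/n2)
- noncentrality = d / SE
- power = probability that a noncentral t with n1 + n2 − 2 degrees of freedom falls outside ± the two-sided 5% critical value t*
- 95% CI half-width = t* × SE

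**Step 1: reproduce the stated figure.** With 25/25, SE = sqrt(2/25) = 0.283 and noncentrality = 0.80/0.283 = 2.83 on 48 df. Two-sided power is 79.1%; the normal approximation gives 80.7%. Both agree with 80% after rounding. A one-sided test gives 87.4%, so the calculation was two-sided with all 25 per group analysed.

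**Step 2: the maximum at week 28.** 34 + 3 = 37. The loss is at least 49 − 37 = 12, or 12/49 = 24.5%. If none of the 3 pending complete, it is 15/49 = 30.6%.

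**Step 3: when the loss occurred.** 49 − 38 = 11 were already missing at week 6, 12 at week 12, and at least 12 at week 28. In net counts, 11 of the 12 losses precede the week 6 assessment.

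**Step 4: the same test with the attainable numbers** (d = 0.80, two-sided 5%).

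| n1/n2 | Power | d at 80% power | CI half-width (SD) |
|---|---|---|---|
| 25/25 (as planned) | 79.1% | 0.81 | 0.57 |
| 26/23 (all randomised) | 78.2% | 0.82 | 0.58 |
| 19/18 | 65.7% | 0.95 | 0.67 |
| 20/17 | 65.5% | 0.95 | 0.67 |
| 22/15 | 64.2% | 0.97 | 0.68 |
| 26/11 (most uneven possible) | 58.0% | 1.04 | 0.73 |
| 17/17 (only 34 seen) | 61.9% | 0.99 | 0.70 |

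For 19/18: SE = sqrt(1/19 + 1/18) = 0.329, noncentrality = 2.43, t* = 2.030 on 35 df, half-width = 2.030 × 0.329 = 0.67. Closing at 49 rather than 50 costs about one percentage point (26/23 row). The rest of the drop comes from missing week 28 data.

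**Step 5: what the mixed model might recover.** This needs the correlation r between baseline and week 28, which the article does not give; the values are assumptions. All figures are for 19/18 and count the help from baseline only.
- Baseline as an adjustment covariate (detectable difference scaled by 1/sqrt(1 − r²)): about 70% at r = 0.3 and 78% at r = 0.5.
- Baseline only as one more outcome time point, with data missing at random (variance per arm (1 − r²)/observed + r²/randomised): about 67% at r = 0.3, 68% at r = 0.5 and 71% at r = 0.7.

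The Aim 1 model lists week 0 among its time points and names no baseline covariate, which is nearer the second case. Most of those lost before week 6 could contribute only baseline to a model on weeks 0, 6, 12 and 28.

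**The case against.** The strongest reply is that nothing was miscalculated. The sentence is conditional on 25 per group, it belongs to the planning stage, and the follow-up counts are reported openly. This stands: a reader might infer an arithmetic error, and there is none. The planned figure should therefore be kept and labelled, not overwritten with one computed from later counts.

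Second, the article already calls itself a feasibility study, puts estimation first and concedes reduced power. This lessens the harm. But the concession carries no number, attributes the reduction to recruitment, which reached 49 of 50, and leaves the power sentence unqualified.

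Third, the planned analysis is a mixed model, and the Discussion claims that regression models are more efficient than unadjusted analyses. This also stands in part. A reader might infer that the trial as analysed has about 65% power. The documents do not support that, because the figure belongs to the unadjusted t test. Nor do they show that the 80% is restored, since the gain depends on an unstated correlation and on how baseline enters the model.

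Fourth, a reader might blame the long unpaid waitlist. The counts do not show it: 11 of the 12 losses precede week 6, and losses by arm are not reported. Some may have left before the week 1 visit, the one kind of loss the sample size is said to have covered. Their number is not given, so the shortfall cannot all be assigned to unplanned later loss.

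**Conclusion.** The concern holds as a missing qualification on a stated power figure. The 80% is right only with complete week 28 data on 25 per group. With at most 37 observed, the article's own test has at most about 66% power for d = 0.80: 64% to 66% for splits from 19/18 to 22/15, 58% at 26/11, and about 62% if only 34 are seen, split evenly. The effect detectable with 80% power moves from about 0.81 to about 0.95, and the half-width from 0.57 to about 0.67 SD.

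These figures rest on a two-sided 5% level, equal variances, no covariate adjustment and assumed arm splits. The ceiling of 37 rests on the October 2021 counts and closed enrolment. The issue bears on how the week 28 result is read; it does not invalidate the design or the planned analysis.

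**What to change.** In the Power Calculation section, keep the 80% and say that it assumes complete week 28 data on all 25 per group. Then add, precision first because estimation is the stated emphasis:

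*With at most 37 participants observed at week 28, an unadjusted two-sided t-test comparison has an expected 95% confidence interval half-width of about 0.67 SD (0.57 SD as planned). On that basis power for d = 0.80 is at most about 66%, lower if the arms are uneven or fewer than 37 are seen, and 80% power is reached for d of about 0.95. The planned mixed model may recover some of this, depending on the correlation between baseline and week 28 and on how baseline enters the model.*

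The Discussion's remark on reduced power should point to these figures and name missing follow-up alongside recruitment. Giving the week 28 numbers by arm, and how many of the 49 left before week 1, would replace the assumed splits and show which losses the replacement rule covered.

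The cost is a few sentences and a less favourable number. No participants, assessments or analyses are added.

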#### Intervention

CBT-I is a comprehensive, multimodal approach that addresses maladaptive cognitions and behaviors that contribute to and maintain sleep difficulties. Treatment consists of education about the 2-process model of sleep (the homeostatic and circadian processes [37]) and their interaction with hyperarousal. Behavioral components of treatment include time-in-bed restriction (also known as sleep restriction [38]), stimulus control [39], and relaxation techniques. The cognitive component of treatment includes identification and modification of maladaptive beliefs and thought patterns about sleep to reduce sleep-related anxiety.

The study treatment protocol was adapted from Edinger’s 4-session, open-source CBT-I manual [40]. Treatment was “front-loaded,” in that Session 1 includes sleep education, stimulus control, and an initial time-in-bed restriction, based on sleep diary data collected in the 1 to 2 weeks prior to the first session. Sessions 2 through 4 are dedicated to adjusting time-in-bed based on ongoing sleep diary data, addressing treatment adherence issues, cognitive therapy, and relaxation skills. Session 4 also includes information about relapse prevention. Treatment is administered by a licensed psychologist or a doctorate-level graduate student trained and supervised by a licensed psychologist. The treatment is outlined in Table 1.

**Table 1 table1:** Session by session outline of brief, telehealth cognitive behavioral therapy for insomnia (CBT-I).

Week	Session	Time	Content
1	1	60 minutes	Review the sleep log and answers provided on the brief sleep assessment. Educate about sleep and basic sleep hygiene instructions. Introduce two-process model of sleep (circadian rhythm and sleep drive) and interfering role of arousal. Determine standard wake time and initial time in bed (TIB) prescription. Provide stimulus control instructions. Answer questions and address concerns. Assign homework.
2	2	30-45 minutes	Review sleep log and adjust TIB prescriptions. Encourage/reinforce adherence. Identify/troubleshoot participant’s problems in adhering to recommended changes in sleep behaviors. Address sleep effort and sleep-related anxiety. Review role of arousal and teach relaxation technique. Answer questions and address concerns. Assign homework.
3 or 4	3	30-45 minutes	Review sleep log and adjust TIB prescriptions. Encourage/reinforce adherence. Identify and troubleshoot the participant’s problems in adhering to prescribed interventions (TIB, relaxation). Address sleep effort and sleep-related anxiety. Answer questions and address concerns. Assign homework.
4 or 5	4	30-45 minutes	Review sleep log and adjust TIB prescriptions. Encourage/reinforce adherence. Identify and troubleshoot the participant’s problems in adhering to prescribed interventions (TIB, relaxation). Address sleep effort and sleep-related anxiety. Discuss relapse prevention. Answer questions and address concerns. Provide instruction on how to continue increasing TIB if desired total sleep time is not yet achieved.

#### Control Condition

We will compare the CBT-I group to a 28-week waitlist control group. Participants assigned to the waitlist control group do not engage in any study interventions while on the waitlist (during the primary assessment period) but complete study assessments at weeks 1-6, 12, and 28. After completion of all primary study time points (28-week follow-up), those assigned to the waitlist control group receive the same 4 telehealth CBT-I sessions delivered over 5 weeks as did the CBT-I group (secondary assessment period). The waitlist control group also completes additional questionnaires during their 4 treatment sessions, but the collected data will not be included in primary analyses.

#### Data Collection

This study is conducted through Stanford Zoom and Stanford RedCap. The Stanford RedCap platform is developed and operated by Stanford Medicine Research Information Technology team. The RedCap platform services at Stanford are subsidized by (1) Stanford School of Medicine Research Office and (2) the National Center for Research Resources and the National Center for Advancing Translational Sciences, National Institutes of Health, through grant UL1 TR001085. All self-reported data are collected through questionnaires built on Stanford RedCap. Data from clinical interviews are entered into RedCap during the interview and then reviewed by the interviewer after the session. Once a participant is deemed eligible by the study team, they are randomized and scheduled for a second Zoom meeting with study staff. At this second Zoom meeting, they are notified of their study arm assignment by a research coordinator and complete week 1 questionnaires. If they are assigned to the treatment group, they meet with the therapist after completing week 1 questionnaires. For each following treatment session (weeks 2-5), participants meet with a research coordinator before meeting with the therapist. At the posttreatment time point (week 6), participants are sent a survey link to complete online questionnaires. If the participant is assigned to the waitlist control group, the week 1 session ends after completing the questionnaires. Participants in the waitlist control group are sent an email with a link to weekly surveys for each subsequent weekly session (weeks 2-6). Once the participant completes the week 1 questionnaires, they are considered enrolled in the study.

#### Recruitment, Enrollment Criteria, Screening, and Retention

Participants are adults in the United States aged 18 years or older who experienced new sleep disturbances after the start of the COVID-19 pandemic. Participants were recruited nationally through online postings, newsletters, and social media. A subset of participants was recruited from an ongoing survey-based observational study about sleep and well-being during the COVID-19 pandemic. All participants met the inclusion and exclusion criteria outlined in Textbox 1.

Interested participants completed online prescreening questions (Table 2) assessing insomnia symptoms before and after the pandemic began (March 1, 2020), insomnia symptom duration, any unstable medications, and seizure history. Participants who met the prescreening criteria (Table 2) were invited to a video call with study staff to further assess eligibility. During this call, a research coordinator explained details of the study procedures and obtained informed consent. Consenting participants and research staff obtaining consent signed the informed consent form via a RedCap survey with e-signature capabilities. Participants were emailed a copy of the signed consent form. After informed consent was obtained, a trained member of the study staff then administered clinical interviews to assess eligibility. Before ending the call, a research coordinator sent the participant a link to complete remaining online screening questionnaires at their own pace. After the participants completed all online screening questionnaires and screening interviews (described in the Measures section), the study team collectively determined if the inclusion and exclusion criteria were met.

During the screening session, sleep disturbance was assessed using the Duke Structured Interview for Sleep Disorders (hereafter referred to as Duke) [41] and ISI. Participants were excluded from the study if their reported sleep disturbance duration on the Duke began prior to the start of the pandemic or if another sleep disorder was primarily responsible for their symptoms. Two versions of the ISI were administered at screening: one assessing symptoms during the week before the pandemic began (past) and one assessing symptoms in the past 2 weeks (current). Participants were deemed eligible for the study if past ISI score was <10 and current ISI score was ≥10, as a score of 10 was found to be optimal in detecting insomnia in a community sample [36].

Participants with current or past psychosis, bipolar disorder, or epilepsy were excluded from the study due to safety concerns. Manipulating sleep increases the risk of seizures [42], mania [43], and psychosis [44] in individuals with a history of these conditions. Further, the brief version of CBT-I utilized in this study has not been validated as a reliable therapy in these populations. We administered the Mini-International Neuropsychiatric Interview (MINI) [45] to screen for psychosis and bipolar disorder and took a basic medical history to screen for history of seizures.

Participants currently abusing substances or taking over-the-counter or prescribed medications for sleep were not permitted in the study. To participate, all other medications must have been stable for at least 3 weeks, and medical conditions must have been deemed stable for at least 3 months by the study clinicians. However, hypnotics and other medications or supplements used to treat sleep disturbance were not permitted to be used during participation in the study. We collected information about current medication use as part of a basic medical history and assessed substance abuse or dependence using the MINI.

For eligible participants, data collected at the screening time point (including surveys after the session) are used as baseline measures.

Criteria for study participation.
**Inclusion Criteria**
Age 18 years or olderHaving access to the internet and an email addressAcute subjective complaint of sleep disturbance (Insomnia Severity Index [ISI] before the pandemic <10 and current ISI ≥10) that began after March 1, 2020 or the COVID-19 pandemic (as reported during interview)Living in the United StatesLiterate and fluent in EnglishWillingness to participate in the study, sign the consent, and complete majority of questionnaires
**Exclusion Criteria**
Presence of suicidal ideation representing high risk as measured by Sheehan-Suicide Tracking Scale (S-STS)Use of medication specifically prescribed for sleep disturbance and unwilling or unable to discontinue more than 1 week prior to baseline data collectionCurrent or lifetime history of bipolar disorder or psychosisCurrent substance abuse or dependenceNot able to verbalize understanding of involvement in research and provide written, informed consentUnstable pharmacotherapy for other mental health disorders (<3 weeks since beginning new medication)Severe impediment to vision, hearing, or hand movement likely to interfere with the ability to complete assessments or are unable or unlikely to follow study protocolsWorking rotating shift that overlaps with midnight

**Table 2 table2:** Prescreening questions and responses indicating eligibility for a screening session.

Prescreening questions	Response criteria for screening session
Are you currently taking any prescribed or over-the-counter sleep medication?	No or willing to discontinue medication prior to enrollment
Have you started a new medication within the last four weeks?	No
How many months have you had trouble sleeping?	Duration indicates symptoms started after the start of the COVID-19 pandemic (March 1, 2020)
Do you have a personal history of epilepsy, convulsions, or seizures?	No
Current Insomnia Severity Index	Total score ≥10
Past Insomnia Severity Index	Total score <10

We employ several precautionary measures to reduce attrition and retain participants. First, at the beginning of the study, participants met with a member of the study team to discuss study procedures and answer questions. Participants are encouraged to ask questions throughout their involvement in the study. Participants were assigned an assessor who administers their clinical interviews at every time point, to encourage familiarity and build rapport with study staff. Participants voluntarily provided multiple different types of contact information (eg, email, phone numbers) for appointment reminders, and sessions are scheduled based on participants’ time preferences. Study staff is persistent in attempting to recontact and engage noncompliant participants. Lastly, study assessments and data collection were carefully designed to minimize barriers to participation. We carefully curated the RedCap database so that participants do not have to re-enter information previously provided, and we eliminated long, superfluous questionnaires. We also added automated features to reduce the need for technical knowledge to navigate the questionnaires.

#### Protection Against Risks

All enrolled participants’ depressive and anxiety symptoms are monitored by a trained clinical psychologist who reviews all adverse events and any significant changes in well-being. Unlike many research studies that recruit locally and conduct study visits in person, the present study enrolls participants across the nation who may suffer from severe depressive symptoms such as suicidal ideation. To address this unique challenge, we developed a robust distressed patient protocol adapted from the 2009 model developed by Draucker et al [46]. Our protocol includes several precautionary measures and multiple levels of assessment and risk classification. Each participant was asked to provide the phone number and email address of an emergency contact during the consenting process. At the start of the first video treatment session, the visit provider confirms the address of the participant’s physical location and has the participant’s local emergency contact personnel readily available at each session. Study staff are trained to recognize signs of distress and indications that the participant may be having thoughts of harm to self or others. If such signs present over the course of the study visit, study staff conduct a formal risk assessment (using the Sheehan-Suicidality Tracking Scale [S-STS] if suicidal ideation is present or a homicide risk assessment if homicidal ideation is present) and determine if the participant is at imminent risk to self or others.

Study staff follow detailed instructions on how to proceed after a determination is made. If imminent threat is not determined, study participants are encouraged to follow up with their own mental health providers and are given contact information for their local emergency room, the National Suicide Prevention Lifeline, and the study psychologist. If imminent risk is determined, a warm transfer is provided to the National Suicide Prevention Lifeline. The visit provider then contacts the study psychologist, and together, they determine if contact of additional parties, including the participant’s emergency contact or local sheriff’s department, is warranted. At each stage, the study psychologist and principal investigator are apprised of steps taken, appropriate documentation is completed, and the institutional review board (IRB) is notified of any adverse events.

In addition to the aforementioned risk mitigation protocol, additional risk management strategies are utilized that leverage built-in, automated systems in RedCap if risk is detected during online survey completion. In RedCap, we established branching logic that automatically classifies subjects as low, moderate, or high suicide risk and sends precomposed emails based on risk level. Participants flagged as low, moderate, or high risk are sent direct emails with study staff contact information, as well as the National Suicide Prevention Lifeline. Those flagged as high risk are also contacted directly by the study psychologist who conducts a full risk assessment via telephone to ensure participant safety to self and others. Emergency contacts or local sheriff’s departments are contacted if a participant is deemed to be high-risk and cannot be directly reached.

